**Figure 2 Fig2:**
[figure not shown]
**Timeline.** EOI, end of intervention; FU, follow- up; IC, informed consent; ICI, initial counseling interview; SOI, start of intervention.

T0: Baseline assessment 1 to 2 weeks before the start of chemotherapy).T1: Start of intervention (SOI).T2: Mid-line (after the first half of the chemotherapy regimen; maximum of 12 weeks).T3: End of intervention (EOI) (after the end of the chemotherapy; maximum 24 weeks).T4: Follow-up, 6 months after the completion of chemotherapy (after maximum of 48 weeks).

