### Sample size and power considerations

Sample size was calculated for the global quality of life (Items 29 and 30 of EORTC-QLQ-C30) and was based on a two-group comparison using Student’s t-test because no reliable estimate of the correlation between repeated measures was available. Following the recommendation by Cocks *et al*. [36], a difference of 10 points between the randomized groups was considered clinically important (that is, ‘smallest medium difference’). This difference corresponds to a standardized effect of d = 0.4 according to Cohen. To detect d = 0.4 with a power of 1 - β = 80% using a two-sample t-test at a two-sided significance level α = 5%, a total of 200 patients in the randomized arms (100 per arm) will be required. The sample size calculation was performed using nQuery Advisor V7.0. We expect the power of the main statistical analysis to be higher than 80% because repeated measurements will be taken into account and the analysis will be additionally adjusted for relevant covariates such as HRQoL at baseline.

We assume that 40% of the patients have no or no strong preference and thus will be randomized. About 60% of the patients are assumed to have a strong preference for the CAM intervention. Therefore, we need to include 200 patients in the randomized arms (100 per arm) and we expect to include about 300 patients in the observational arms. Assuming up to 15% of patients may not have primary outcome data available, the sample size was adjusted to a total of 236 patients in the randomized arms (118 per arm) and about 354 patients in the observational arms.

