A linear mixed model will be used to compare HRQoL under chemotherapy between the two randomized groups from treatment start to long-term follow-up (T1 to T4). This model takes into account the hierarchical structure of the data with repeated measurements nested in patients (that is, patients will be included as random effects in the intercept). Fixed effects will include treatment (usual nursing care versus complex nursing care intervention on CAM), the time of measurement (T1 to T4), the interaction of treatment and time, as well as the HRQoL baseline scores at T1, and the stratification variables stage of cancer (non-metastatic versus metastatic) and study centre (university hospital versus community hospital). Because the measurements are not equidistant in time, an unstructured covariance matrix will be estimated. For the main effect of treatment, the null hypothesis of no difference in group averages will be tested at the two-sided significance level of α = 0.05. Differences between short-term and long-term effects will be assessed by the interaction of treatment and time. The primary analysis will be performed for all randomized patients according to the intention-to-treat principle. As sensitivity analysis, the analysis will be repeated in the per protocol set, excluding patients with major protocol violations. Because longitudinal mixed models make use of the missing at random assumption, no imputation will be used to handle missing data in the primary analysis. However, sensitivity analyses will be conducted to assess the impact of missing data (for example, omitted measurements at some time point) by various approaches, including for example the ICA-r method (imputation according to reasons for missingness [62]), the last observation carried forward, and multiple imputation. Model fit will be assessed by visual inspection of residual plots. Descriptive analyses of secondary endpoints will be performed. All estimates will be presented with 95% confidence intervals. External validity will be assessed by comparing the randomized with the non-randomized patients. The comparison of the observational group will thereby facilitate the applicability of the results. The central part of the second analysis step is, thus, to assess whether treatment effects observed in the randomized patients are comparable with those observed in the two observational arms. If there are measurable differences between these two groups with regard to prognostic factors, the effect of these differences will be examined using propensity score methods. Propensity scores will be determined that reflect the patients’ preferences.

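### With the T1 score as a covariate and no imputation allowed, randomized patients who have later scores but no T1 score drop out of the primary model, so the stated analysis set is not delivered

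*Protocol article*

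**What the plan says.** Three statements stand together in the Data analysis section of the protocol article:

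- On the analysis set: "The primary analysis will be performed for all randomized patients according to the intention-to-treat principle".
- On the model: the fixed effects are treatment, time, their interaction and the stratification variables, "as well as the HRQoL baseline scores at T1".
- On missing data: because longitudinal mixed models rest on missing at random, "no imputation will be used to handle missing data in the primary analysis".

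The section then lists sensitivity analyses for missing data. They include imputation according to the reason for missingness, "the last observation carried forward, and multiple imputation".

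The Sample size section inflates the target for losses: "Assuming up to 15% of patients may not have primary outcome data available".

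On timing, Table 1 lists the first EORTC-QLQ-C30 at T1, labelled both baseline and start of intervention, and none at T0. The timeline below Figure 2 describes T0 as "Baseline assessment 1 to 2 weeks before the start of chemotherapy" and T1 as the start of the intervention. The Recruitment and randomization section places baseline assessments after consent and then describes allocation.

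**The concern.** A likelihood-based mixed model can use a patient with some outcome scores missing, because her remaining rows still contribute. It cannot use a row whose covariate value is missing. The T1 score is one value per patient, carried on all her rows, so its absence removes every row she has. The justification given for not imputing does not reach this case.

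The patient affected is a randomized woman who missed the T1 form, or left the global quality-of-life items blank so that no score can be formed, but returned T2, T3 or T4. Followed literally, the plan discards her observed outcomes, and the primary analysis no longer covers everyone randomized. At stake are some precision and, if the T1 form is filled in after allocation is known, possibly a loss that differs between arms.

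**Working it through.** **1. The plan's own figures.** Inputs from the Sample size section: d = 0.4, two-sided alpha 5%, power 80%, 1:1 allocation, 15% without primary outcome data.

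- The two-sample t-test needs 99.08 per arm, rounded up to 100. Power at 100 per arm is 80.4%.
- Inflation: 100 / (1 - 0.15) = 117.6, so 118 per arm and 236 in total.

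Both stated figures, 200 and 236, reproduce.

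**2. Who stays in the model.** Illustrative set of 236 randomized patients with assumed gaps: 5 gave no data at all, and 13 missed only the T1 form.

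| Model, nothing imputed | Patients used |
|---|---|
| T1 as covariate, responses T2 to T4 | 236 - 5 - 13 = 218 |
| T1 as covariate, responses T1 to T4 | 218 |
| T1 as response only, no T1 covariate | 236 - 5 = 231 |

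The 13 are lost because of the covariate, whether or not T1 is also a response. The 5 are lost under every model in the table.

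**3. Possible size.** The protocol gives no rate of missing T1 scores, so the rates m below are assumptions. The second column is 236 × m. The other columns take the case in which the T1 losses are additional to the 15%: n per arm = 118 × 0.85 × (1 - m), with noncentrality 0.4 × √(n/2).

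| m | Of 236 | n per arm | Noncentrality | t-test power |
|---|---|---|---|---|
| 2% | 4.7 | 98.3 | 2.80 | 79.7% |
| 5% | 11.8 | 95.3 | 2.76 | 78.4% |
| 10% | 23.6 | 90.3 | 2.69 | 76.2% |

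If the T1 losses instead fall within the 15%, 236 × 0.85 = 200.6 patients remain, about 100 per arm, and power is at least 80%.

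**4. Do the sensitivity analyses repair it?** Multiple imputation could restore these patients, but it is named only as a sensitivity analysis. The test at the 5% level is made on the reduced set. Last observation carried forward cannot supply a T1 score from T0, because Table 1 schedules no HRQoL assessment there.

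**5. Order of T1 and allocation.** The Recruitment section can be read as placing the baseline form before allocation. The timeline gives the baseline label to T0 and makes T1 the start of the intervention, which permits allocation before T1. Table 1 gives T1 both labels. The text does not settle the order.

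**The case against.** The strongest reply is that handling a missing baseline value is a matter for the statistical analysis plan, which is not shown, and that the article nowhere says such patients are excluded. The no-imputation sentence is argued from how mixed models treat repeated outcomes, so it may have been meant for outcomes only. That would settle the matter had the protocol been silent. It is not: the rule is stated for missing data in general. An analysis plan that filled in T1 would depart from it, and one that obeyed it would break the stated analysis set.

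Other parts of the reply stand and limit the point:

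- A reader might infer that the primary analysis is not intention-to-treat. The protocol does not support that. Patients are analysed in the arm to which they were randomized, losses are planned for, and missing-data sensitivity analyses are named.
- A reader might add patients who withdraw before T1 and return nothing later. They have no outcome and are absent from any likelihood analysis without imputation, so the covariate is not the cause. The fix below does not recover them either.
- A reader might infer bias between arms. That requires T1 to follow allocation, which is unsettled. If T1 comes first, a missing form is a gap from before randomization and unrelated to arm.
- A reader might infer a definite shortfall in power. The 15% allowance may already include T1 losses, since Table 1 lists the T1 questionnaire under the primary outcome. The plan also expects the adjusted repeated-measures analysis to exceed the power of the t-test. With an assumed baseline-outcome correlation of 0.3, even the 10% case gives 2 × 90.3 / (1 - 0.09) = 198 effective patients, close to the 200 required.

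**Conclusion.** The point holds in a limited form. The stated analysis set, the T1 covariate and the general ban on imputation cannot all be honoured once a randomized patient has later scores but no T1 score. As written, she is dropped and her observed outcomes are lost.

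The number affected cannot be determined from the protocol. About 5 to 24 of 236 rests on an assumed T1 missing rate of 2% to 10%. A fall in t-test power below 80% rests on the further assumption that these losses add to the 15%. The consequence is mainly lost precision if T1 precedes allocation. A loss that differs by arm is possible only if T1 follows it. The wording should be changed, but nothing here shows that the randomized comparison is invalid.

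**What to change.** Change the wording in the Data analysis section:

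1. Limit the no-imputation rule to outcome values.
2. Fill a missing T1 covariate without regard to arm, for example with the mean T1 score pooled over both arms. Use the filled value as a covariate only, never as a response.
3. Describe the primary set as all randomized patients with at least one post-baseline HRQoL score, and report by arm how many had none.

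It would help to state in the same place whether the T1 form is completed before or after randomization, since that decides whether missing T1 scores could be related to arm. An alternative that also keeps these patients is to model T1 as a response with a common baseline mean and drop it as a covariate.

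The cost is a few sentences and no new data. The downside is slightly weaker baseline adjustment for the few patients whose T1 score is filled in.

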### Objectives

The primary outcome of the CONGO study is cancer patients’ HRQoL. It will be assessed if cancer patients, starting a new chemotherapy regime, benefit from a complex nursing care intervention, consisting of a CAM intervention packet (for example, aromatherapy, massage, compress, acupressure), counseling on self-help CAMs, and evidence-based informational material on CAM, regarding HRQoL in comparison to patients receiving usual nursing care.

Secondary outcomes are to assess the effects of the complex intervention on a wide range of physical and psychosocial symptoms including nausea, fatigue, pain, anxiety/depression, social support, self-efficacy, patient competence, spiritual wellbeing, patient satisfaction, and the quality of life of patients’ significant others (SOs). Furthermore, accompanying research on health economic outcomes will be conducted.

In addition, the acceptability and feasibility of the complex intervention will be evaluated in the two recruiting centers by providing a thorough process evaluation and information about the provision of integrated cancer care in outpatient cancer services. Therefore, quantitative data will be collected that will be supplemented with qualitative interview data involving healthcare staff, patients, and their SOs.

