**Secondary outcomes**								
Nausea	MAT				X			
Fatigue	FACIT-F		X			X	X	X
Pain (general)	VAS		X			X	X	X
Anxiety, depression	PHQ-9		X			X	X	X
Social support	F-SozU K-14		X				X	X
Self-efficacy	SES6G		X			X	X	X
Patient competence	FEPK 2-57		X				X	X
Spiritual wellbeing	Sp-REUK-15		X				X	X
Patient satisfaction	EORTC-QLQ-PATSAT32						X	
Accompanying research (health economy)	Mannheimer Modul RV		X			X	X	
Quality of life SOs	WHOQOL-BREF		X				X	X
	CQOLC		X				X	X
**Others** Socio-demographic factors		X						
Cancer characteristics		X						
Medical history		X						
Treatment data			X		X	X	X	X

*EOI* end of intervention, *FU* follow-up, *PD* patient diary, *SOI* start of intervention, *SO* significant other.

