In contrast to efficacy studies, the current effectiveness study will consider several elements when analyzing participants’ HRQoL. The intervention targets common symptoms of patients undergoing chemotherapy. To address these symptoms, a range of CAM interventions will be administered to the patient in the outpatient centre at each cycle of chemotherapy. Some of these CAM interventions are already part of the clinics’ nursing standards [20]; however, they have not yet been standardized and evaluated. In the current study, the patients will also receive counseling on how to apply some of these CAM interventions at home between cycles. Plus, patients will receive an evidence-based information booklet on different CAM interventions as well as contact sources on other external CAM providers in case they prefer to pursue the wide CAM spectrum further on. As a chemotherapy regimen lasts very long (for example, 24 weeks) the patient will visit the outpatient clinic every 3 to 4 weeks that is, 6 to 8 times. It is likely that the patient builds a relationship with the assigned CAM nurse caring for her, which might also add to improvements in HRQoL. In the randomized group, we can account for potential confounders, and analyze the primary and secondary outcomes, but we cannot explain which single element of the interacting intervention agents has the highest impact on changes in HRQoL.

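### Secondary endpoints get only a descriptive analysis, although most have a T1 value that would allow the baseline-adjusted mixed model planned for the primary endpoint

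*Protocol article*

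**What the plan says.** The Objectives section gives the secondary outcomes a comparative purpose: "Secondary outcomes are to assess the effects of the complex intervention on a wide range of physical and psychosocial symptoms". Table 1 schedules most of them at T1 and again later. Fatigue, pain, PHQ-9 and self-efficacy are taken at T1, T2, T3 and T4. Social support, patient competence, spiritual wellbeing and the significant others' quality of life are taken at T1, T3 and T4. Two have no T1 value: nausea (MAT, in the diary once per cycle) and satisfaction (PATSAT32, at T3 only). The health-economic module has its own analysis section and is left aside here.

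In Data analysis, the primary endpoint gets a linear mixed model with a random patient intercept, treatment, time and their interaction, "as well as the HRQoL baseline scores at T1, and the stratification variables stage of cancer (non-metastatic versus metastatic) and study centre". Missing data are left to the missing-at-random property of that model. The secondary endpoints get one sentence, followed by a general one: "Descriptive analyses of secondary endpoints will be performed. All estimates will be presented with 95% confidence intervals". No estimator, covariate or missing-data rule is named for them.

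The Discussion adds: "In the randomized group, we can account for potential confounders, and analyze the primary and secondary outcomes".

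**The concern.** The method named for the secondary endpoints is weaker than the aim set for them and weaker than the data permit. The Abstract uses the same word as a contrast: a linear mixed model for the randomized comparison, a descriptive analysis for the observational part. On that usage, the secondary endpoints would be summarized by arm at each visit, without the T1 score or the strata.

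Two things would be at stake. The first is precision. Where T1 predicts the later score, a comparison of raw follow-up means leaves explainable variance in the error term and carries any chance baseline difference into the estimate. The plan accepts this argument for the primary endpoint: it expects power above 80% partly because "the analysis will be additionally adjusted for relevant covariates such as HRQoL at baseline". The second is missing visits. A mean over those who returned the form at a visit makes no use of the other visits of patients who missed it, whereas the primary model does.

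**Working it through.** **The plan's own figure.** Inputs from Sample size and power considerations: d = 0.4, power 80%, two-sided 5%, 1:1 allocation.
- Normal approximation: n per arm = 2(1.96 + 0.8416)² / 0.4² = 2 × 7.849 / 0.16 = 98.1, so 99.
- Exact t-test: 99.1, so 100 per arm, with power 80.4%.
- Allowance for 15% missing: 200 / 0.85 = 235.3, so 236.
- Total: 236 / 0.40 = 590, of which 354 are observational.

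All of these agree with the article.

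**Precision at one follow-up visit.** Take 100 evaluable patients per arm and work in SD units of the instrument. The baseline-outcome correlation ρ is an assumption: the article says it had no reliable estimate of the correlation between repeated measures. The range shown is 0.3 to 0.7.
- Raw follow-up means: half-width = 1.96 × √(2/100) = 0.277 SD.
- Change from T1: 0.277 × √(2(1 − ρ)).
- Adjusted for T1: 0.277 × √(1 − ρ²).

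| ρ | Raw means | Change score | T1-adjusted | Narrower than raw | Narrower than change |
|---|---|---|---|---|---|
| 0.3 | 0.277 | 0.328 | 0.264 | 5% | 19% |
| 0.5 | 0.277 | 0.277 | 0.240 | 13% | 13% |
| 0.7 | 0.277 | 0.215 | 0.198 | 29% | 8% |

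The percentages do not depend on n. They therefore also apply to the significant-other outcomes, whose sample size the article does not give. In sample-size terms, ignoring T1 costs a fraction ρ² of the patients: 9%, 25% or 49%.

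**Strata.** If stage and centre explain a share R² of the variance, the width is multiplied by √(1 − R²). For assumed R² of 0.02, 0.05 and 0.10 this is 0.990, 0.975 and 0.949, a gain of 1% to 5%.

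**Missing visits.** The article allows for up to 15% of patients without primary outcome data, includes patients under palliative treatment as a stratum, and places T4 at up to 48 weeks. If return of a form depends on earlier scores, and the effect of this does not cancel between the arms, visit-wise available-case differences are biased. A mixed model that uses the earlier scores is valid under missing at random. The article gives no figures from which to size this.

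**The case against.** The strongest reply is that the article never says adjustment is omitted. Descriptive may simply mean non-confirmatory: only the primary endpoint has a test at a stated alpha. The article calls the analysis of the observational part descriptive too, yet Data analysis foresees propensity score methods there, so the word need not mean raw summaries. The Discussion sentence on accounting for confounders can be read as pointing towards adjustment of the secondary outcomes. A condensed article also commonly leaves the secondary-endpoint model to the full protocol or analysis plan. This stands as far as intent goes: a reader might infer that the plan commits to unadjusted comparisons, and the text does not support that. It does not remove the point. The primary model is set out in full, the secondary endpoints are given a different and weaker label, and nothing says that the model extends to them.

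A reader might also infer that the T1 score is thrown away. That does not follow either, because a descriptive analysis can report change from T1. This is why the gain against change scores is shown as well.

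Nor can the width be turned into a loss of power without more assumptions. The effect d = 0.4 was set for the EORTC global scale, and the secondary endpoints are neither powered nor tested.

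Finally, with complete data randomization protects an unadjusted comparison from confounding, so chance baseline imbalance costs precision and does not bias the estimate in expectation. This is correct. The missing-visit argument is separate from it and conditional on the dropout pattern.

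**Conclusion.** The point holds as a low-severity improvement to exploratory endpoints, not as an error. No stated figure is wrong, and the sample size reproduces.

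If the sentence is applied literally, the 95% intervals for secondary outcomes with a T1 value are wider than they need be. Adjustment would narrow them by about 5%, 13% or 29% against raw means at ρ of 0.3, 0.5 or 0.7, and by 19%, 13% or 8% against change scores. Nearly all of this comes from the T1 score, and the strata probably add little. The handling of missing visits would also be weaker than for the primary endpoint, by an amount that cannot be sized from the article.

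The conclusion rests on the literal reading and on assumed correlations. If an adjusted model was intended all along, only the wording needs to change.

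**What to change.** Replace the sentence on secondary endpoints with wording such as: 'Secondary endpoints measured at T1 and later will be estimated in the randomized patients with the same form of linear mixed model as the primary endpoint, with post-baseline scores as the response and with the T1 score of that instrument, stage of cancer and study centre as fixed effects in addition to treatment, time and their interaction. MAT and PATSAT32, which have no T1 value, will be adjusted for the stratification variables only. Adjusted differences with 95% confidence intervals will be reported as exploratory.'

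The cost is the wording and a few extra model fits. No new data, visits or patients are needed, and the secondary endpoints keep their non-confirmatory status.

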**Methods/design:**

CONGO is a prospective partially randomized patient preference (PRPP) trial including adult women diagnosed with breast and gynecologic cancer starting a new chemotherapy regimen. Patients without strong preferences for CAM will be randomized to usual nursing care or complex nursing care; those patients with strong preferences will be allowed their choice. The intervention consists of three interacting and intertwined elements: CAM nursing intervention packet, counseling on CAM using a resource-oriented approach and evidence-based informational material on CAM.

Primary outcome data on participants’ HRQoL will be collected from baseline until the end of treatment and long-term follow-up using the EORTC-QLQ-C30. Secondary outcomes include nausea, fatigue, pain, anxiety/depression, social support, self-efficacy, patient competence, spiritual wellbeing, and satisfaction with care. Accompanying research on economic outcomes as well as a mixed-methods process evaluation will be conducted.

A total of 590 patients (236 patients in the randomized part of the study and 354 patients in the observational part of the study) will be recruited in the two outpatient clinics. The first analysis step will be the intention-to-treat (ITT) analysis of the randomized part of the trial. A linear mixed model will be used to compare the continuous primary endpoint between the intervention and control arm of the randomized group. The observational part of the trial will be analyzed descriptively. External validity will be assessed by comparing randomized with nonrandomized patients.

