The shift from inpatient to outpatient cancer treatment has increased awareness of patients’ self-care strategies and also of their significant others (SOs) including family members and close friends [74,75]. Cancer has become a family disease affecting not only the individual with the cancer diagnosis, but also involving their SOs who often are experiencing high levels of distress [76] while accompanying and supporting their loved one going through the treatment stages and adjusting to a new life situation [77]. A strength of the current study is the consideration of patients’ SO, whose QoL will be assessed T1, T3, and T4; and who will be interviewed during the process evaluation to gain a better understanding about their perceptions on the cancer patient’s experiences with the complex nursing care intervention on CAM. The interventions have been primarily composed for the patient receiving chemotherapy, and therefore exclude couple-based methods; however, some of these home-based interventions can be administered by the SOs (for example, preparing the tea, conducting the massage). Thus, the current study will provide further information in highlighting if the shared CAM use contributes to bonding and improvements of QoL in cancer patients’ SOs [74,75].

A further strength of the CONGO study is the interprofessional aspect, which takes into account the collaboration between health professionals in the design of the study as well as in the composition of the complex nurse-led intervention. To our knowledge, this is one of the first nurse-led CAM intervention studies in Germany that can assess nurses’ relevant contribution in promoting HRQoL during cancer therapy.

Another unique aspect of the CONGO study is patients’ choice of the study arm. Due to high interest and prevalence of CAM in cancer populations, we expect that 60% of participants will decide for the intervention and will therefore be allocated into the observational study arm. This study arm will be analyzed descriptively and will be used to assess the external validity of the study results. However, it will be a challenge to recruit enough participants for the randomized arm.

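### The second analysis step needs a usual-care preference arm, but the planning figures and the allocation rule leave that arm empty

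*Protocol article*

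**What the plan says.** After the randomized analysis, the Data analysis section plans a second step whose central aim is "to assess whether treatment effects observed in the randomized patients are comparable with those observed in the two observational arms". It adds propensity scores reflecting preference, to be used if randomized and non-randomized patients differ in prognosis.

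The planning figures are under Sample size and power considerations: "We assume that 40% of the patients have no or no strong preference and thus will be randomized", and "About 60% of the patients are assumed to have a strong preference for the CAM intervention". From these the section derives that "we expect to include about 300 patients in the observational arms", which becomes, after allowance for missing outcomes, "a total of 236 patients in the randomized arms (118 per arm) and about 354 patients in the observational arms". The Discussion repeats the assumption and speaks of a single arm: "we expect that 60% of participants will decide for the intervention and will therefore be allocated into the observational study arm".

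The operational rule is under Recruitment and randomization. The nurse places a woman in the observational part if she strongly prefers the CAM intervention, and all remaining participants are randomized.

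Other sections describe a wider choice. The Background says that preferences both for and against the intervention are considered. Design of the study lets women with strong preferences choose. Control group refers to usual-care patients in the observational part as well as in the randomized part.

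**The concern.** A treatment effect is a contrast between CAM and usual care. To compare the randomized effect with an observational one, the observational part must contain both treatments. The planning figures put all of it on CAM, and the allocation rule gives a woman who strongly prefers usual care no route into it. Propensity scores can rebalance two groups that exist, but they cannot supply outcomes for a group with no members.

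At stake is what the trial can say from its 354 non-randomized women, 60% of the total. If the second step stays as worded, the report will either lack its central comparison or rest a statement of comparable effects on a very small, self-selected usual-care group.

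**Working it through.** **Inputs.** From Sample size and power considerations: difference 10 points, d = 0.4, two-sided 5%, 80% power, 15% without primary outcome data, 40% randomized, about 60% preferring CAM. From the Abstract: "A total of 590 patients (236 patients in the randomized part of the study and 354 patients in the observational part of the study". The SD is implied: 10 / 0.4 = 25.

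**Reproducing the plan's figures.**
- A two-sample t-test with d = 0.4 needs 99.08 per arm, so 100 per arm and 200 in total.
- 200 / 0.85 = 235.3, so 236 randomized.
- 236 / 0.40 = 590 in total.
- 0.60 × 590 = 354 observational (before the allowance: 200 / 0.40 = 500, and 0.60 × 500 = 300).

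**Expected usual-care preference arm.** Observational total minus women preferring CAM: 354 − 0.60 × 590 = 0, or 300 − 0.60 × 500 = 0 before the allowance. The shares leave 100% − 40% − 60% = 0%. The article gives no other expected number for this arm.

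**If a few such women enter.** Their number is an assumption. Take 300 evaluable observational patients, of whom n chose usual care, with SD 25 and no adjustment.
- SE of the observational effect = 25 × √(1/n + 1/(300 − n)).
- SE of the randomized effect = 25 × √(2/100) = 3.54.
- SE of the difference between the two effects = √(SE_obs² + 3.54²).

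| n on usual care | SE_obs | 95% half-width, observational effect | 95% half-width, difference between effects |
|---|---|---|---|
| 15 (5% of 300) | 6.62 | 1.96 × 6.62 = 13.0 | 1.96 × √(6.62² + 3.54²) = 14.7 |
| 30 (10% of 300) | 4.81 | 1.96 × 4.81 = 9.4 | 1.96 × √(4.81² + 3.54²) = 11.7 |

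Taking the share from all 590 women instead, with 354 observational in total and 15% missing, gives:

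| Share of 590 | Recruited on usual care | Half-width, observational effect | Half-width, difference between effects |
|---|---|---|---|
| 1% | 6 | 21.9 | 23.0 |
| 2% | 12 | 15.6 | 17.1 |
| 5% | 30 | 10.1 | 12.3 |
| 10% | 59 | 7.6 | 10.3 |

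**Effect of baseline adjustment.** With an assumed baseline correlation of 0.5, each half-width shrinks by √(1 − 0.25) = 0.866. In the first table, 14.7 becomes 12.7 and 11.7 becomes 10.1. At 10% of 590, 10.3 becomes 8.9. Propensity weighting would usually work in the opposite direction.

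**What one observational arm supports.** Randomized CAM (100 evaluable) against preference CAM (300 evaluable): 1.96 × 25 × √(1/100 + 1/300) = 1.96 × 2.89 = 5.7 points, unadjusted.

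**The case against.** The strongest defence is that about 60% is a rounded planning figure and not a cap, and may loosely describe everyone with a strong preference in either direction. The Background, Design of the study and Control group sections all provide for women who choose usual care, the observational arms are mostly written in the plural, and the flow chart that may show them is not reproduced. This stands as far as it goes: usual-care choosers may appear, and the effect would then be estimable, at 30 of 300 to within 9.4 points. A reader might infer that the contrast can never be estimated; the documents do not support that. They do show one set of sections at odds with another, and the wider wording supplies neither an expected number nor an entry route under the recruitment rule.

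It is also fair that the plan already includes a general comparison of randomized with non-randomized patients and a descriptive analysis of the observational part, so external validity does not rest on this contrast alone. The Data analysis section nevertheless calls the contrast central.

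Two stronger readings should be resisted. A reader might infer that external validity is the main reason for the preference design, so that the design fails in its purpose. Design of the study gives at least equal weight to keeping pleased or disappointed patients from distorting the quality-of-life assessment. A reader might also take "If there are measurable differences between these two groups with regard to prognostic factors" as a formal pre-test that decides whether confounding is adjusted for. No test is described, and the groups meant can be the randomized and non-randomized patients.

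**Conclusion.** The point holds as a contradiction within the protocol. The second step presupposes two observational arms, while the sample size section, the Discussion and the recruitment rule together give one of them an expected size of 0. The zero follows from the document's own shares and needs no outside assumption.

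The precision figures do rest on assumptions: the number of usual-care choosers, SD 25 at a single time point, and no adjustment. In every unadjusted scenario shown, the half-width for the difference between effects exceeds the 10-point relevant difference (10.3 to 23.0). Covariate adjustment would narrow it somewhat and, at the largest share considered, could bring it just below 10. A claim that the effects are comparable would therefore have weak support unless the usual-care preference arm were considerably larger than planned.

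The randomized comparison, its sample size and its model are unaffected. The matter should be corrected before the second step is analyzed, but it does not threaten the primary result.

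**What to change.** 1. Reconcile Recruitment and randomization, Sample size and power considerations and the Discussion with the Background, Design of the study, Control group and Data analysis. State whether a woman who strongly prefers usual care can enter the observational part, by what route, and how many are expected.
2. Restate the second step as what one observational arm can support: randomized CAM against preference CAM on global HRQoL at T2 to T4, with prespecified propensity or covariate adjustment. Describe it as a comparison of outcomes under the same treatment. It mixes preference with case mix and does not test whether treatment effects agree.
3. Report a within-observational treatment effect, and any statement that effects are comparable, only if the usual-care preference arm reaches a prespecified minimum size. Otherwise describe that arm only.

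The cost is a revision of the analysis and recruitment wording and a narrower external-validity claim. The revised second step needs no additional patients or assessments.
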